### Telephone group

Participants randomised to the telephone group will receive regular phone contact from the research dietitian. An initial assessment will be completed over the phone, with subsequent weekly or fortnightly phone reviews depending on the therapist perception of participant’s needs. Any contact in addition to these scheduled reviews is permissible and will be documented, for example if the participant calls the dietitian with an urgent nutritional issue. Total time spent in conversation with participants will be documented, to allow for a cost analysis between intervention groups (see below).

If a participant is unavailable for a scheduled phone review, the research dietitian will attempt to arrange a more convenient time for the participant. In the event of a second instance that a participant is unavailable in the same week, then no intervention will occur that week. This will be documented, as will the reason for the participant’s unavailability (if known).

### mHealth group

Participants will be provided with a tablet computer (e.g. iPad) and 6 months wireless connectivity if they do not already have access to this equipment. Access to a tablet computer will enable patients to provide fortnightly (or weekly) reports to their dietitian regarding their weight, nutrition impact symptoms (e.g. diarrhoea, mucositis, and nausea) and oral intake so their dietitian can be informed and develop management options prior to their subsequent review via electronic messages. The focus of these consultations is to implement individually tailored, symptom-directed nutritional behavioural management program. Participant engagement in self-monitoring their weight, nutrition impact symptoms, and oral intake using the tablet computer aims to empower and motivate change in dietary behaviours that may be contributing to poor health outcomes [19]. The iPad tool also enables the patient and their carers access to electronic resources that support the nutrition advice.

Communication will be facilitated by a mobile App called MyPace. MyPace has been designed for dietetic practice that supports patient-practitioner relationships [25, 26]. Initial phone contact will occur at baseline to set up the electronic system and complete an initial nutrition assessment. Automated daily reminders will be sent via MyPace to promote behaviour change and adherence. Weight, nutrition impact symptoms (e.g. diarrhoea, mucositis, and nausea) and oral intake will be monitored electronically, and oral nutritional supplements will be recommended as required.

### Adherence

In the event that the research dietitian does not receive any messages or contact from the participant for over a week, the dietitian will make phone contact to confirm that there are no technical issues. Further technical education will be given to the participant as required. The dietitian will not discuss nutritional topics via phone with the participant at any point other than the initial assessment, instead they will encourage the participant to make contact via electronic messages. Total amount of time spent in contact with the participant will be documented, for a cost analysis between intervention groups. This time will be described as nutritional or technical.

### Control group

A usual care, control condition will be used and no additional nutritional advice from the research team will be provided to the participants (Table 2).

**Table 2 Tab2:** The key points of difference between the intervention groups and usual care control group

1. When nutrition services commence (immediately post-diagnosis versus ~ 12 week delay). 2. The mechanism of access (universal vs referral-based). 3. The mode of service delivery (non face-to-face vs face-to-face). 4. The regularity of service provision (at least fortnightly versus ad hoc, “as required” inpatient basis). 5. The ability to focus on addressing problems before they arise rather than reacting to problems that may already be established.	

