The prevalence of malnutrition at time of diagnosis for people with upper gastrointestinal cancer is as high as 90% in some studies [15]. Early and intensive nutritional intervention can improve nutritional status and Quality of Life (QoL) in both upper gastrointestinal and head and neck cancer patients undergoing radiotherapy [15, 16]. A retrospective review reported on the effect of a nutrition pathway commenced at presentation to a multidisciplinary oesophageal cancer clinic identified that those who received earlier nutritional treatment had significantly greater radiotherapy completion rates (92% vs. 50%), fewer hospital admissions (75% vs. 46%), shorter hospital stays (3.2 days vs 13.5 days) and experienced overall less weight loss (4.2 Kg vs. 8.9 Kg) [8]. A systematic review with meta-analysis evaluated if oral dietary interventions, in people with cancer (any location) who were malnourished or at risk of malnutrition, improved nutritional indices as well as quality of life (QoL) and survival [17]. No effect of oral nutrition intervention was found on mortality (at 6 months). Aspects of QoL were reported to be improved including the global QoL score, and some functional and symptom scale measures. The effects on body weight and other nutrition measures were inconsistent. Overall this review found that there was limited high quality evidence and that more was needed to determine the optimal timing, duration and intensity of nutrition intervention in cancer patients.

To optimise nutritional outcomes, a tailored person-centred approach and frequent review by a dietitian before and during the cancer treatment period is desirable. Novel cost-effective approaches to deliver early, pre-hospital nutrition intervention before current usual care services are commenced, are needed. Linking clinicians and patients via mobile health (mHealth) and wireless technologies is a contemporary solution not yet tested for delivery of nutrition therapy to people with cancer. Research into consumer and practitioner use of, and attitudes towards, integrating technology into healthcare suggests that the right application may be positively accepted by both sets of users [18, 19]. Further, healthcare systems in Europe, Australia and the United States are currently actively encouraging and investing in technological innovations to support available routine care [20, 21].

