### Randomisation and blinding

Permuted block randomisation with stratification (two groups) will be employed by a biostatistician who is independent of the investigator team. Groups will be stratified based on a malnutrition risk score using the Malnutrition Screening Tool (MST) [23]. The MST is a quick and simple nutrition screening tool based on weight loss and appetite changes. Stratification will be based on a score of < 3 or ≥ 3 as this is routinely used by the supportive cancer care nurse practitioners at the outpatient clinic of Victorian tertiary hospitals for automatic referral to the dietetic outpatient clinic. Computer-generated random numbers are determined in STATA version 14 (StataCorp LP, College Station, Texas, USA). Block sizes will be randomly varied and permuted by the computer software and an initial seed value (a number used to initialize number generation) set for reproducibility. Researchers conducting recruitment, data collection, and data analysis will be blinded to group allocation.

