### Usual care

All participants will receive usual care, regardless of group allocation. Standard inpatient dietetic services will be provided subsequent to this using a tailored, symptom-directed approach by a registered dietitian specialising in oncology. This is typically face-to-face counselling with a hospital-based dietitian following medical referral at the commencement of treatment (i.e admission for surgery or chemotherapy commencement). Patients who attend an outpatient service are screened for nutritional risk via MST [23] whereby a score of equal to or greater than three will result in a referral to a hospital dietetic outpatient clinic. The frequency and duration of these sessions will vary on a case-by-case basis. Oral nutritional supplement samples will be supplied if clinically indicated as is consistent with usual care at participating sites.

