### Contamination and co-intervention

Participants in the control arm may seek other sources of dietary advice above what is offered as usual care and obtain oral supplements, which are freely available. Contamination may also be possible (i.e control group participants seek additional dietetic input) if participants enrolled in the study are admitted to the same hospital and allocated beds in the same room as participants in the intervention arms. Participants will be asked to self-report on any nutrition/dietetics information or services they may have accessed during the study period that was additional to the study or usual care services.

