### Economic evaluation analysis

A trial-based, cost-utility analysis will be undertaken to understand what the cost per quality adjusted life year gained is of each intervention group relative to the control group. This economic evaluation will be conducted from the societal perspective over a 12 month follow-up horizon. It will take the form of an incremental cost-utility (cost per quality-adjusted life year gained) analysis. Bootstrap replications of the trial dataset will be used to generate a 95% confidence ellipse surrounding the cost-utility point estimate, and to inform cost-utility acceptability curve analyses. One-way sensitivity analyses will be used to investigate the stability of the main trial finding to variation in key clinical and economic inputs. Exploratory analyses will be undertaken to identify potential intervention interaction effects with age, confidence to use and pre-existing use of iPad/smart phone.

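### Table 2 gives every control a delay of about 12 weeks, but usual care automatically refers outpatients with MST ≥3 to a dietitian, and the plan does not measure how much earlier care started

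*Protocol article*

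**What the plan says.** **Control condition.** Table 2 (Control group section) sets out the differences between intervention and control as single statements for the whole control group. Item 1 is "When nutrition services commence (immediately post-diagnosis versus ~ 12 week delay". Item 2 is "The mechanism of access (universal vs referral-based". Item 4 describes control care as ad hoc and inpatient.

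**Usual care.** This section describes two routes. On the usual one, "This is typically face-to-face counselling with a hospital-based dietitian following medical referral at the commencement of treatment". The other applies to patients who attend an outpatient service: they are screened with the MST, and "a score of equal to or greater than three will result in a referral to a hospital dietetic outpatient clinic". Randomisation and blinding says the same cut-off is in routine use at Victorian tertiary hospitals "for automatic referral to the dietetic outpatient clinic", and makes it the stratification factor. Usual care goes to all three arms.

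**Measurement.** The self-report item under Contamination and co-intervention covers dietetic services "that was additional to the study or usual care services". Economic outcomes captures outpatient services by self-report and, where accessible, medical records, in order to value costs. Database extractions plans ongoing hospital extraction. None of these names the date of first dietitian contact.

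**Analysis.** The primary model lists baseline utility, age, gender, PG-SGA category and cancer location. The exploratory interactions are "potential intervention interaction effects with age, confidence to use and pre-existing use of iPad/smart phone". The MST stratum is in neither list.

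**The concern.** An outpatient referral triggered by a screening score is neither inpatient care nor tied to the start of treatment, so the two descriptions of control care do not agree. They differ along the line used to stratify randomisation: controls with MST <3 may wait as Table 2 says, while controls with MST ≥3 have a route to a dietitian that could open much sooner.

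The trial's aim includes starting nutrition care earlier than usual. If the achieved difference in start time is not recorded, a null result cannot be told apart from a weak timing contrast, and a positive result could be reported as a 12-week head start that some controls did not experience.

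**Working it through.** **1. The passages side by side**

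| Feature of control care | Table 2 | Usual care; Randomisation and blinding |
|---|---|---|
| Start | about 12 weeks' delay | start of treatment (typical), or outpatient referral on MST ≥3 |
| Setting | inpatient, as required | inpatient and dietetic outpatient clinic |
| Access | by referral | medical referral, or automatic on MST ≥3 |

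Only the access row agrees. The outpatient route matters in practice because Recruitment draws partly on weekly outpatient clinic lists. Patients who have had urgent surgery are also eligible, and surgical admission is one of the usual triggers for dietetic care, so some participants in any arm may have seen a dietitian before randomisation.

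**2. Size of the affected group.** Not stated. Background says "The prevalence of malnutrition at time of diagnosis for people with upper gastrointestinal cancer is as high as 90% in some studies" and describes weight loss as a common presenting concern. The MST scores weight loss and appetite, so a small MST ≥3 share would be surprising, but malnutrition prevalence is not that share.

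**3. Mean head start (illustration).** Let p be the share of controls with MST ≥3 and w their wait in weeks. Assume all of them use the outpatient route and all others wait 12 weeks. Mean = 12(1 − p) + pw.
- p = 0.5, w = 2 to 4: 6 + 1 = 7 to 6 + 2 = 8 weeks.
- p = 0.9, w = 2 to 4: 1.2 + 1.8 = 3.0 to 1.2 + 3.6 = 4.8 weeks.
- w = 12, any p: 12 weeks, no loss.

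Both p and w are assumed.

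**4. The plan's sample size.** Inputs from Sample size calculation: standardised difference 0.70, 80% power, alpha 0.05 (taken as two-sided). n = 2(1.960 + 0.842)² / 0.70² = 32.04, rounded up to 33 per group. A two-sample t-test at n = 33 has 80.0% power. The stated figure is reproduced.

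**5. Possible dilution (illustration).** Put the 0.70 in the MST <3 stratum and a fraction r of it in MST ≥3. Pooled d = 0.70[(1 − p) + pr]; power = Φ(d√(33/2) − 1.960). On this formula d = 0.70 gives 81%.

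| p | r | pooled d | power |
|---|---|---|---|
| 0.3 | 0.75 | 0.65 | 75% |
| 0.3 | 0.5 | 0.595 | 68% |
| 0.5 | 0.75 | 0.61 | 70% |
| 0.5 | 0.5 | 0.525 | 57% |
| 0.5 | 0 | 0.35 | 30% (t-test 29%) |
| 0.7 | 0.5 | 0.455 | 46% |
| 0.7 | 0 | 0.21 | 13% |

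**6. Can a stratum comparison carry the conclusion?** The standard error of an arm-by-stratum interaction with 33 per arm is √[2/(33p) + 2/(33(1 − p))]. At p = 0.5 this is 0.492. Power is 11% for a difference between strata of 0.35 and 30% for 0.70. At p = 0.3 or 0.7 the standard error is 0.537 and power is about 10% and 26%. It cannot.

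**The case against.** The best defence is that this is a trial of a package against usual care. The hypothesis concerns an early and intensive service added to usual care, and variation in usual care belongs to such a comparator. Usual care reaches all arms and randomisation is stratified on MST, so the pooled estimate is not biased. All of this stands.

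A reader might go further and infer that there is no head start for MST ≥3 controls. The article does not support that. A referral is not a visit, no waiting time is given, only patients attending an outpatient service are screened, the 12 weeks may be an average, and Table 2 itself calls control access referral-based.

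A reader might also want to rest the early-care conclusion on MST <3. That would not isolate timing: Table 2 lists mode, regularity and anticipatory focus as further differences, and these apply in both strata.

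The power illustrations can fairly be challenged. The 0.70 was set for comparisons with the whole control group, and nothing in the article suggests zero benefit in MST ≥3.

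Finally, interactions and extraction fields are often left to an analysis plan or full protocol, and PG-SGA category, already in the model, partly reflects the same risk. That weakens any complaint about omissions taken alone. It does not remove the disagreement between Table 2 and Usual care, nor the fact that the one self-report item on dietetic services is worded to leave out usual care.

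**Conclusion.** The point holds as an inconsistency in the description of the control condition, together with a measurement gap that follows from it. For controls with MST ≥3 the head start may be much shorter than 12 weeks. How much shorter, and for how many, cannot be derived from the article.

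The primary comparison remains valid for intervention plus usual care versus usual care. The limitation is in interpretation: as described, the trial could not report how much earlier care began. A mean head start anywhere from 3.0 to 12 weeks fits the assumed inputs above. Pooled power runs from 75% down to 13% in the cases tabulated, and stays at the planned level if the effect does not differ by stratum. These figures show sensitivity and are not estimates for this trial.

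**What to change.** (a) Reconcile Table 2 with Usual care and with Randomisation and blinding, and describe the control condition separately for MST <3 and MST ≥3. Which description reflects practice is for the investigators to establish.

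(b) Record the date of first dietitian contact and the number of usual-care dietetic contacts in all three arms. The hospital extraction already planned is the better source, because it keeps this topic out of the blinded interviews. Report the achieved head start by arm and MST stratum.

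(c) Include the MST stratum in the primary model, since it is the randomisation stratum. Report stratum-specific effects as exploratory, and do not tie the main conclusion to MST <3.

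The cost is two extraction fields and one further analysis on a variable already collected. Records will be incomplete at some sites, and stratum estimates will be imprecise with 37 recruited per group.

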### Data collection

The primary method of data collection at each of the four time points (baseline, three, six and 12-months) will be via telephone or face-to-face interview with a blinded researcher. Participants will also be given the option to self-complete and return the questionnaires (described in the outcome sections) to the researcher, via email, stamped and self-addressed envelope, or in person in an inpatient or outpatient setting. These data will be entered into a coded, de-identified spreadsheet. To promote retention, participants will be reminded at each follow-up of the next planned data collection point. It will be explained why these data collection points are important to the study outcomes despite the conclusion of the active intervention period.

### Contamination and co-intervention

Participants in the control arm may seek other sources of dietary advice above what is offered as usual care and obtain oral supplements, which are freely available. Contamination may also be possible (i.e control group participants seek additional dietetic input) if participants enrolled in the study are admitted to the same hospital and allocated beds in the same room as participants in the intervention arms. Participants will be asked to self-report on any nutrition/dietetics information or services they may have accessed during the study period that was additional to the study or usual care services.

### Primary outcome

The primary outcome for this study is quality adjusted life years lived. This will be calculated using the EQ-5D-5 L instrument [27] (as preferred by the UK National Institute for Health and Clinical Excellence [28]) using the area under the curve calculation approach. An area-under-the-curve approach will be used to convert serial EQ-5D-5 L measures into a single estimate of quality-adjusted life years lived following recruitment for each participant. Participants who pass away during the follow-up period will be given a utility value of zero from the date of death onwards. The EQ-5D-5Linstrument is one of the most widely used, generic utility instruments internationally. This instrument has been found to have superior psychometric properties (particularly a lower proportion of participants reporting a “ceiling” score of perfect health and correlation with other measures of health-related quality of life) compared to the EQ-5D-3 L version when used in oncology populations [29] and in non-cancer populations [30]. We will use an EQ-5D-3 L crosswalk value set to generate utility values at each time point before converting to a Quality Adjusted Life Year (QALY) lived estimate [31].

### Secondary outcomes

We will use the EORTC-C30 scale as a secondary measure of health related quality of life [32]. We have included this tool along with the EQ-5D-5 L as it is a disease-specific quality of life instrument that includes items within several domains that are specific to an oncology population. This tool contains 30 items which are separated into domain scores for global health status, physical function, role function, emotional function, cognitive function, social function, fatigue, nausea and vomiting, pain, dyspnoea, insomnia, appetite loss, constipation, diarrhoea, and financial difficulties. This scale has been shown to have high construct validity, ability to differentiate populations with and without cancer, convergent validity with other health state questionnaires, and high test-retest reliability [32, 33].

Nutritional status will be measured using the Patient-Generated Subjective Global Assessment (PG-SGA) tool. This tool is widely used and has been shown to have reliable clinometric properties when used in the oncology population [34, 35]. The first section of the PG-SGA focuses on four areas and when able, is completed by the participant: weight and weight history, food intake history, nutrition impact symptoms, and activities of daily living and function. The researcher will also complete the second section which incorporates specific disease and its relation to nutritional requirements, metabolic demands, and a physical examination to determine loss of subcutaneous fat and muscle wasting if face-to-face data collection is possible.

Other secondary outcome measures include survival over the 12 month follow up period and changes in self-reported body weight. Where possible (if face-to-face data collection is possible) we will measure waist circumference and hand grip strength using a hand dynamometer (Jamar Digital Hand Dynamometer, Lafayette, Indiana, USA) to support our data relating to changes in nutritional status. For the same reason, tissue density from CT scans taken as routine care pre and 3 month post treatment will be analyzed at the 3rd lumbar vertebra to determine body composition (skeletal muscle, visceral and subcutaneous fat) using Slice-O-Matic software (v.5.0; Tomovision, Montreal, Quebec, Canada).

